In addition, during a defined period, he or she will collect individual patient data on a subset of 20 % of included patients to identify risk factors for MRSA carriage based on history taking (notion of previously recorded MRSA carriage, transfer from other department or hospital, transfer from a nursing home, hospital stay in the previous year, attending outpatient care at a clinic in the previous year, presence of chronic skin sores, or living/working in a livestock farm, working as veterinarian or in a slaughterhouse). These data will be analysed to estimate the predictive value of these risk factors for the carriage of MRSA.

In the control arm, as per routine infection control policy in each institution, all patients admitted to study wards and presenting with will be sampled within 24 h after admission by taking swabs of anterior nares, throat, perineum and of any wounds, bladder catheter or intravenous catheter exit site (see appendix 1 for conventional MRSA screening procedures). Patients with previously recorded active MRSA carriage will be presumptively placed in contact isolation until three new series of conventional selective cultures of relevant body sites are found negative.

In the rapid test intervention arm, all patients admitted to study wards will be sampled within 24 h after admission. To ensure comparison of like with like, sample taking will include: (1) a swab from the anterior nares for PCR testing according to the test manufacturer’s instructions (see appendix 2 for rapid PCR screening test procedure); (2) the swab of anterior nares, and swabs from throat, perineum and of any wounds, bladder catheter or intravenous catheter exit site will be processed by conventional testing (see appendix 1 for conventional MRSA screening procedures). Patients with previously recorded active MRSA carriage will not be sampled for PCR testing but placed in pre-emptive isolation until three series of conventional selective cultures of relevant body sites are found negative.

Thus, patients in each arm will be managed identically, except that the rapid PCR test will be performed and its results made immediately available to infection control and clinical staff in the intervention arm.

MRSA isolates will be tested for mupirocin susceptibility and stored at -80°C for genotyping.

Additional contact isolation precautions.

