**Study endpoints and statistical analysis**

The **primary endpoint** of the study will be the following microbiologically documented outcome:

1. **Incidence density rate of MRSA nosocomial colonisation**, defined as the number of new cases of hospital-acquired MRSA (first positive culture > 48 h after admission) divided by the number of patient days at risk (defined as cumulated lengths of stay by patients who stayed ≥ 3 days and were MRSA negative on admission screening by conventional culture, and, if performed, PCR test).

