**Secondary endpoints**

These will include three related process of care indicators:

1. Time (h) between admission and notification of MRSA positive culture/PCR
2. Time (h) between admission and placement of newly detected MRSA carrier in contact isolation

Secondary endpoints will also include the following microbiologically-documented outcomes:

1. Number of patient-days of MRSA positive patients cared for with standard precautions and not isolated
2. Cumulative incidence of MRSA nosocomial colonisation, defined as number of new cases of hospital-acquired MRSA (first positive culture >48 h after admission) divided by the number of admitted patients who stayed ≥ 3 days and were MRSA negative on admission by culture and PCR testing, if performed.
3. Cumulative incidence of MRSA nosocomial infection, defined as number of new cases of hospital acquired MRSA infection (according to CDC definitions for nosocomial infection and with first MRSA positive culture > 48 h after admission) divided by number of admitted patients who stayed ≥ 3 days.
4. Number of clusters of ≥ 2 cases/unit of acquired MRSA colonisation with a clonally related strain, defined as a MRSA strain with the same spa type or PFGE major type.
5. Sensitivity and specificity of rapid PCR test compared to conventional culture for MRSA screening, taking into account one parallel set of admission nasal screening samples per patient.

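### The at-risk set for MRSA acquisition excludes patients on a PCR result that only the intervention arm has, so the primary endpoint's population depends on allocation

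*Protocol*

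**What the plan says.** The primary endpoint (Protocol, Study endpoints and statistical analysis) is an incidence density.

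- **Numerator:** "number of new cases of hospital-acquired MRSA (first positive culture > 48 h after admission".
- **Denominator:** days at risk of patients who stayed at least 3 days and "were MRSA negative on admission screening by conventional culture, and, if performed, PCR test".
- **Cumulative incidence (Secondary endpoints):** the denominator repeats the rule, taking patients who "were MRSA negative on admission by culture and PCR testing, if performed".

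Intervention study design sets out the admission tests.

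- **Control arm:** patients are "sampled within 24 h after admission by taking swabs of anterior nares, throat, perineum" and at wound and catheter sites, for culture only.
- **Intervention arm:** a nasal PCR is added, and the nasal and other swabs "will be processed by conventional testing (see appendix 1 for conventional MRSA screening procedures". The sampling is introduced with "To ensure comparison of like with like, sample taking will include".
- **Difference between arms:** management is said to be identical "except that the rapid PCR test will be performed and its results made immediately available".

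Among the process indicators, the first is "Time (h) between admission and notification of MRSA positive culture/PCR".

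**The concern.** Both arms should apply the same test for who is at risk. Here the control arm uses one test (culture) and the intervention arm uses two (culture and PCR).

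Consider a patient colonised on admission whose admission culture is negative, who stays at least 3 days and who is culture-positive after 48 h. In the control arm this patient is a nosocomial acquisition. In the intervention arm, if PCR was positive, the patient is outside the at-risk set. On the reading that cases come from that set, the patient is not counted at all. The rate can therefore differ between arms without any difference in transmission.

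Nothing else in the design removes this. After the crossover each ward still has PCR in only one of its two periods, so the artefact sits inside every ward's treatment contrast. The adjustment variables in the primary Poisson model are at ward level and cannot repair selection of individual patients.

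Time to notification has a related problem. Patients positive by PCR only can enter it in one arm alone, so the two medians describe different populations.

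**Working it through.** The protocol states no figure for this bias, so there is none to reproduce. Its sample size does not enter the calculation.

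**1. Inputs**

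- Incidence *I*, in cases per 100 admissions: 0.79% observed at baseline and its upper confidence limit 1.55% (Addendum 1); 3% planned (Sample size estimate).
- Culture sensitivity *Se*: 95-100% at 42-48 h for some chromogenic media (Introduction).
- Assumed, not in the protocol: new carriers on admission *p* = 3-8%; share of missed carriers with a positive culture after 48 h *d* = 50-80%; share of those caught by nasal PCR *c* = 50-70%.

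**2. Formula.** With no true effect, and with cases counted within the at-risk set:

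removed = *p* × (1 − *Se*) × *d* × *c*, and null rate ratio = (*I* − removed) / *I*.

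This treats *I* as the rate a culture-only arm would show. It ignores the small change in denominator and assumes similar stays, so that the ratio carries over to incidence density.

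**3. Cases removed per 100 admissions**

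- Middle case, low: 5% × 5% × 50% × 50% = 0.0625.
- Middle case, high: 5% × 5% × 80% × 70% = 0.14.
- Largest in range: 8% × 5% × 80% × 70% = 0.224.
- Smallest: culture sensitivity 100% gives 0.

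**4. Null rate ratio**

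| Incidence | Middle case | Largest in range |
| --- | --- | --- |
| 0.79% | 1 − 0.14/0.79 = 0.82 to 1 − 0.0625/0.79 = 0.92 | 1 − 0.224/0.79 = 0.72 |
| 1.55% | 0.91 to 0.96 | 0.86 |
| 3% | 0.95 to 0.98 | 0.93 |

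The upper limit is 1.00 throughout.

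**5. In cases.** With 2 × 1,850 = 3,700 patients per arm pooled, the control arm expects 3,700 × 0.79% = 29 cases. The middle case removes 3,700 × 0.0625% = 2.3 to 3,700 × 0.14% = 5.2 from the intervention arm.

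**6. False finding at 0.79%.** For the high middle case the rates are 0.79% and 0.65%. The standard error is √[(0.0079 × 0.9921 + 0.0065 × 0.9935)/3,700] = 0.00197, so the shift is 0.0014/0.00197 = 0.71 standard errors. The chance of a result significantly favouring PCR is P(Z > 1.96 − 0.71) = 11%, against a nominal 2.5%. The low middle case gives 5%. Clustering is ignored.

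**7. Literal reading.** If the PCR condition limits only the denominator, every case stays in the numerator while PCR-positive, culture-negative patients lose their days. At the preliminary PCR specificity of 97% (Introduction), about 3% of culture-negative patients would go. With similar stays, the null rate ratio is about 1/0.97 = 1.03, against PCR.

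**8. Time to notification.** With PCR sensitivity 98.5% and specificity 97%, the culture-negative share of PCR-positives is (1 − *p*) × 0.03 / [(1 − *p*) × 0.03 + *p* × 0.985]. At 5% prevalence this is 0.0285/(0.0285 + 0.04925) = 37%; at 10% it is 22% and at 3% it is 50%. The protocol does not describe the reference standard behind these preliminary figures, so the share negative on multi-site culture may differ.

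**The case against.** **Size.** The study's culture method is a strong one: chromogenic agar read to 48 h, broth enrichment and several body sites (Appendix 1). A reader might infer a much larger bias. A culture sensitivity of 90% with 8% carriers gives 1 − (8% × 10% × 80% × 70%)/0.79% = 0.43. The protocol does not support that input, since it gives 95-100% for some media at 42-48 h. Discharge-culture compliance was 68% at baseline, though improving (Addendum 1), so detecting 80% of missed carriers later is optimistic. A nasal PCR may also miss carriage at other sites. All of this stands, and the effect is small at high culture sensitivity or higher incidence.

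**Direction.** A reader might infer that the bias always favours PCR. The text does not establish that, because the PCR condition is attached to the days at risk and not to the case definition. Counting cases within the at-risk set is the natural reading, but it is an inference.

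**Process endpoints.** A reader might extend the problem to all three, in PCR's favour and with every PCR-only patient notified fast. Only time to notification names PCR. For time to isolation and non-isolated days it is an inference, supported by the rule that isolation follows detection by either test. For non-isolated days, extra PCR-only carriers can add days in the intervention arm, which works against PCR. Fast notification is not assured either: sampling may take up to 24 h and PCR runs in working hours.

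**Remedy.** PCR-positive patients are isolated and decolonised even when culture-negative (Additional contact isolation precautions). Under a culture-only at-risk set, true carriers among them may be culture-negative at discharge because they were treated, while equivalent control patients still count as acquisitions. This stands as a limit of the fix.

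None of these points defends a definition that differs by arm. That both versions can be computed from the planned data is a reason to choose the arm-neutral one in advance.

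**Conclusion.** The concern holds. The at-risk set for the primary and cumulative incidence endpoints depends on allocation, and the protocol does not say clearly whether the PCR condition also limits the cases.

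The likely direction is in favour of PCR. The size is uncertain and probably modest: a null rate ratio of 0.82-0.92 in the middle case at 0.79% incidence, moving towards 1 at higher incidence. These figures rest on assumed admission prevalence, later detection and PCR yield, none of which the protocol gives. The low baseline incidence is what allows a few misclassified patients to matter.

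For time to notification the mismatch of populations follows from the wording. For the other two process endpoints it is an inference, with the direction open for non-isolated days.

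**What to change.** - For the primary and cumulative incidence endpoints, define admission-negative status by conventional multi-site admission culture alone, in both arms.
- State that numerator cases must come from that same at-risk set.
- In the time-to-notification, time-to-isolation and non-isolated-days endpoints, restrict carriers to those confirmed by admission culture in both arms.
- Report the PCR-inclusive definition as a sensitivity analysis.

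The cost is endpoint wording only: the same cultures are already taken in both arms, and neither the samples nor the sample size changes. One limitation should be stated. PCR-positive, culture-negative patients who are isolated and decolonised stay in the intervention at-risk set, so some asymmetry at discharge culture remains. For missed carriers it acts on the same patients as the present artefact, and would be as large only if decolonisation suppressed every later positive culture.

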**Secondary endpoints**

These will include three related process of care indicators:

1. Time (h) between admission and notification of MRSA positive culture/PCR
2. Time (h) between admission and placement of newly detected MRSA carrier in contact isolation

Secondary endpoints will also include the following microbiologically-documented outcomes:

1. Number of patient-days of MRSA positive patients cared for with standard precautions and not isolated
2. Cumulative incidence of MRSA nosocomial colonisation, defined as number of new cases of hospital-acquired MRSA (first positive culture >48 h after admission) divided by the number of admitted patients who stayed ≥ 3 days and were MRSA negative on admission by culture and PCR testing, if performed.
3. Cumulative incidence of MRSA nosocomial infection, defined as number of new cases of hospital acquired MRSA infection (according to CDC definitions for nosocomial infection and with first MRSA positive culture > 48 h after admission) divided by number of admitted patients who stayed ≥ 3 days.
4. Number of clusters of ≥ 2 cases/unit of acquired MRSA colonisation with a clonally related strain, defined as a MRSA strain with the same spa type or PFGE major type.
5. Sensitivity and specificity of rapid PCR test compared to conventional culture for MRSA screening, taking into account one parallel set of admission nasal screening samples per patient.

The **primary analysis** will be based on Poisson regression two level model (individual patient and unit exposure) performed at each hospital level to assess the impact of the intervention on local incidence-density of MRSA nosocomial colonisation, and ajusted for four potentially confounding factors. The dependent variable will be endpoint 1 above. The ward level **independent variables** will include (1) **intervention arm**, (2) MRSA **colonisation pressure** (as determined by monthly proportion of MRSA colonisation-days/total patient-days among patients admitted during the preceding month in one particular ward), (3) **staff** **compliance with standard and isolation precautions** (as determined by a sample of 50 observations per ward/ trial period, including 25 care opportunities for patients under MRSA isolation precautions and 25 for patients cared for with standard precautions; see appendix 6 for precautions compliance monitoring procedure) (4) **antibiotic use** (as determined by cumulated number of Defined Daily Doses of J01 ATC class of antimicrobial drugs per monthly period) and (5) monthly bed occupancy rate.

Heterogeneity of effect by ward/hospital will be assessed. **To quantify the protective efficacy of the intervention** for the at risk population per centre, the adjusted Rate Ratio (and 95% confidence interval) of nosocomial MRSA acquisition will be calculated for the intervention arm in all study wards per hospital. Pooled analysis of average effect for both hospitals will be calculated. In case of significant heterogeneity between hospitals, hospital level will be added as covariate in the model.

**Secondary analyses** will include:

A. Logistic regression two level models (individual patient and unit exposure) will be performed at each hospital level to assess the impact of the intervention on local cumulated incidence of MRSA nosocomial colonisation. The dependent variable will be endpoint 6 above. The **independent variables** will include patient age, sex and the 5 independent ward level indicators as described above for the primary Poisson analysis.

Heterogeneity of effect by ward/hospital will be assessed. Pooled analysis of average effect for both hospitals will be calculated. In case of significant heterogeneity between hospitals, hospital level will be added as covariate in the model.

C. The median process time intervals (endpoints 2-4 above) and number of missed isolation days (endpoint 5 above) will be compared by Wilcoxon tests for patients within the same unit/hospital between arms; median times (interquartile range) will be compared for each study phase and hospital.

D. In addition, monthly rates of endpoints 1, 6 and 7 will be plotted over time and interrupted time-series, segmented linear regression analysis of temporal trends per study periods will be performed for each hospital. The hypothesis to be tested is that there will be a significant drop in the level of rates from the beginning of the intervention compared to the baseline or control period, possibly associated with a negative change of slope due to a decreasing trend in the intervention period.

E. Diagnostic accuracy (clinical sensitivity and specificity) will be calculated for the rapid PCR test (MRSA GeneXpert, Cepheid) compared to conventional culture as gold standard based on all matched nasal swabs (N=3,700) tested in parallel during the 10 month trial period.

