MRSA contact isolation precautions will be applied to hospitalised patients as per local policy (see appendix 3 for isolation procedures in HE and AZSJ hospitals) either when previously recorded in the laboratory information file as active MRSA carrier or as soon as newly detected by either culture or PCR. Patients will be released from isolation after three consecutive culture screens for MRSA are negative after the end of therapy. Topical decolonisation therapy will be applied as per routine protocol in each institution (see appendix 4 for decolonisation procedures in HE and AZSJ hospitals) to all patients with either a positive MRSA culture and/or PCR.

Notification of screening results and process time recording.

Results of MRSA screening tests will be notified electronically to clinicians by either the technologist or biologist on duty through the laboratory information system (LIS) as well as with a telephone call to the Infection Control study nurse (during working hours) or the unit head nurse (outwith working hours). For culture tests, both presumptive positive results based on colony pigmentation typical for MRSA on chromogenic selective culture medium as well confirmed identification results will be notified immediately by the same communication modes. The precise timing (date, hour, min) of all telephonic result notifications will be recorded in the LIS.

The date and time (hour; min) of patient admission to study ward, as well as of patient placement in contact isolation or release from isolation will be recorded by the infection control study nurse. The date and time (hour; min) of screening sample reception in the laboratory, as well as of result electronic notification will be recorded by the LIS.

Primary outcome monitoring and case finding procedures.

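### Carrier status for the process-time endpoints and the at-risk set rests partly on a PCR run in one arm only; one culture-based rule for both arms is a cheap improvement

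*Protocol*

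**What the plan says.** Under Secondary endpoints, the protocol lists two process times and a count of unisolated days:

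- "Time (h) between admission and notification of MRSA positive culture/PCR"
- "Time (h) between admission and placement of newly detected MRSA carrier in contact isolation"
- "Number of patient-days of MRSA positive patients cared for with standard precautions and not isolated"

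The paragraph on additional contact isolation precautions, under Intervention study design, isolates patients "as soon as newly detected by either culture or PCR" and gives decolonisation "to all patients with either a positive MRSA culture and/or PCR". A positive PCR alone is therefore enough to make a patient a newly detected carrier.

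PCR is done in the intervention arm only. In that arm the nasal swab is also cultured, and "swabs from throat, perineum and of any wounds, bladder catheter or intravenous catheter exit site will be processed by conventional testing". The control arm has the same culture set.

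Secondary analysis C compares median times, and the "number of missed isolation days (endpoint 5 above) will be compared by Wilcoxon tests for patients within the same unit/hospital between arms", with interquartile ranges. Secondary analysis E assesses PCR "compared to conventional culture as gold standard based on all matched nasal swabs (N=3,700").

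The primary endpoint's at-risk population consists of patients negative on admission culture and also, where it was done, on PCR. The cumulative-incidence endpoint uses the same rule. The numerator is defined by a first positive culture more than 48 hours after admission.

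**The concern.** A patient who is PCR-positive with all admission cultures negative is a case in the PCR arm, notified and isolated quickly. The same kind of patient in the control arm is never identified and is absent from the comparison. The two arms are then compared on differently selected patients, although the stated aims concern carriers and the protocol takes parallel cultures so that like can be compared with like.

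The same selection touches the primary endpoint, because these patients leave the at-risk set in one arm only.

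At stake is how far the reported gain in speed reflects earlier isolation of carriers, and how far it reflects isolation of patients with no positive culture. As the plan stands, such patients are visible only in the nasal specificity figure, which gives no isolation-days or decolonisation courses.

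**Working it through.** **Which endpoints are affected.** For time to notification the inclusion of PCR-only patients is explicit. For time to isolation it follows from the isolation paragraph. For unisolated days it is inferred, because the protocol does not say which test makes a patient MRSA-positive.

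**Inputs from the protocol.** There are 1,850 patients per arm in each hospital (Sample size estimate), so 2 × 1,850 = 3,700 PCR-arm patients, which reproduces the N in secondary analysis E. Preliminary sensitivity is 98.5% and specificity 97% (Introduction; sample site not stated). Unisolated stay is expected to fall from 3 to 0 days (Study design). Baseline acquisition is 0.79% (Addendum 1).

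**Assumed.** The prevalence p of newly detected, culture-positive carriage is not given. I use 3%, 5% and 10%.

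**Number and share.** Culture-positive cases C = N × p. PCR-only patients D = N × (1 − p) × (1 − specificity). Share of PCR-arm cases = D / (C + D).

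| p | C | D at 97% | Share | D if half are culture-positive elsewhere | Share | D at 98% (assumed) | Share |
|---|---|---|---|---|---|---|---|
| 3% | 111 | 107.7 | 49.2% | 53.8 | 32.7% | 71.8 | 39.3% |
| 5% | 185 | 105.5 | 36.3% | 52.7 | 22.2% | 70.3 | 27.5% |
| 10% | 370 | 99.9 | 21.3% | 50.0 | 11.9% | 66.6 | 15.3% |

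For example, 3,700 × 0.97 × 0.03 = 107.7, and 107.7 / 218.7 = 49.2%. The counts at 97% are an upper guide, since some nasal-negative patients will be culture-positive at another site and known carriers are not PCR-tested. The shares do not depend on N.

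**Effect on the planned summaries.** Suppose each case has either 0 or 3 days' delay, and nasal PCR finds a fraction s of culture-positive carriers. The slow share is 1 − s among culture-positive carriers and (1 − s) × C / (C + D) as written.

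- Median: adding PCR-only patients can move it from slow to fast only if s is below 50%.
- Upper quartile: it can move only if s is below 75%. At an assumed s of 70%, the slow share goes from 30% to 15.2%, 19.1% or 23.6% (p = 3%, 5%, 10%), so the quartile moves from 3 days to 0. At p = 10% it does not move if half of D are culture-positive elsewhere (0.30 × 370 / 420 = 26.4%) or if specificity is 98% (0.30 × 370 / 436.6 = 25.4%).
- At s = 98.5%, the slow share is 1.5% before any dilution, and neither summary changes.

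**Unisolated days.** Per-patient values fall when near-zero patients are added. A total of patient-days can only rise.

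**Primary endpoint.** At 0.79%, 3,700 × 0.0079 = 29.2 control cases. Remove 108 patients from the PCR-arm denominator only, and assume equal stays and no true effect.

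- If cases need not come from the at-risk set: rate ratio = 3,700 / 3,592 = 1.03.
- If they must, and x of the excluded patients later grow MRSA: rate ratio = ((29.2 − x) / 3,592) / (29.2 / 3,700), which is 0.92 at x = 3 and 0.85 at x = 5. The values of x are assumed.

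**The case against.** The strongest reply is that these are process-of-care indicators. The hospitals isolate and decolonise on either test, so timing everyone whom the strategy flags describes care as delivered. A culture rule also denies PCR credit for true carriers that culture missed. This stands as a reason to keep the present definition as a sensitivity analysis. It does not make the arms comparable, because the control arm has no means of identifying the same patients.

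It can also be said that presumptive culture positives are notified before confirmation, so unconfirmed positives are not peculiar to PCR. That is true, but it happens in both arms and creates no difference between them.

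Three stronger readings are tempting and not supported:

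- A reader might infer that the gain is overstated by the dilution of the mean, (C + D) / C, which is 1.27 to 1.97 at 97% specificity. The plan reports medians and interquartile ranges with Wilcoxon tests, not means.
- A reader might infer that the upper quartile will hide carriers whom PCR misses. That needs PCR to find fewer than 75% of carriers, a figure found nowhere in the protocol, and even at 70% it fails in some of the scenarios above.
- A reader might infer that the primary result is biased towards PCR. The ratios of 0.92 and 0.85 rest on assumed counts, and under the other reading of the numerator the bias is about 1.03, against PCR.

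**Conclusion.** The point holds as a cheap improvement. The written definitions select cases, and at-risk patients, partly by a test run in one arm, when a common yardstick is already collected in both. Up to about 100 to 108 PCR-arm patients are involved, some 21% to 49% of that arm's cases at an assumed prevalence of 10% to 3%, and fewer if some are culture-positive at other sites.

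The direction of the process-time result is not in doubt, and the medians change little if nasal PCR finds most carriers. The effect on the interquartile range and the Wilcoxon comparison depends on prevalence and PCR sensitivity, both unknown here. For unisolated days the problem is one of ambiguous wording, and its direction depends on whether per-patient values or a total is reported. For the primary rate ratio, the direction depends on whether cases are drawn from the at-risk set, and the size cannot be fixed from the documents.

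**What to change.** 1. In Secondary endpoints, for both process times and the unisolated days, take as cases in both arms the newly detected patients with a positive admission culture at any site. Run the first time to the first notification by PCR or culture, and the second to placement in isolation. This keeps PCR's speed advantage. Retain the present either-test definition as a sensitivity analysis.
2. In the primary endpoint and the matching cumulative-incidence endpoint, define at-risk patients by negative admission culture in both arms and draw the numerator from that set. Retain the present definition as a sensitivity analysis.
3. Tabulate separately the patients who are PCR-positive with all admission cultures negative, giving their number, isolation-days and decolonisation courses.

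The cost is small. No new samples are needed: admission cultures are taken in both arms, and notification and isolation times are already recorded. The downside is that true carriers found by PCR but missed by culture get no credit in the main process comparison. They remain visible in the separate table and the sensitivity analysis.

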# ULB-Hopital Erasme*, and Department of Statistics, ULB-School of Public Health**, Bruxelles

# and AZ StJan***, Brugge

## Sponsors:

## Federal Public Service Public Health, Food Safety and Environment, Belgium.

## Cepheid, Europe.

## Introduction

Methicillin-resistant *Staphylococcus aureus* (MRSA) strains have become endemic pathogens in acute and chronic healthcare facilities in Belgium and are also spreading in the community. MRSA infection is causing increased public concern as it carries a significant risk of morbidity, mortality and has been linked to substantial excess healthcare costs (1). The increased risk of prolonged hospital stay and fatal outcome from bloodstream or surgical infection with MRSA, as compared with no infection or infection with methicillin-susceptible *S.aureus*, has been well documented (1).

Efficient control of MRSA transmission within healthcare facilities critically depends on screening for and isolation of MRSA carriers among admitted patients. Active surveillance cultures for MRSA are now part of clinical practice recommendations both in Europe and the USA (2-3). Indeed, studies have indicated that up to 70 % of the patient reservoir for MRSA among hospitalized patients can only be detected by active sampling and selective cultures of muco-cutaneous colonization sites, including the nares, throat, skin, wounds, rectum and insertion sites for invasive devices. MRSA colonization places the individual patient at increased risk of healthcare associated infection and constitutes a reservoir for transmission to other hospitalized patients. There is an urgent public health need for early and reliable detection of carriers of MRSA among patients admitted to healthcare facilities, to inform patient isolation and decontamination procedures, and thereby more effectively control cross-infection (4).

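### The infection endpoint mixes two populations: on the plain reading, patients with a positive admission culture stay in the denominator but cannot be cases

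*Protocol*

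**What the plan says.** Under Secondary endpoints, the third microbiologically documented outcome is the cumulative incidence of nosocomial MRSA infection. Its cases meet the CDC definition and the timing rule "with first MRSA positive culture > 48 h after admission) divided by number of admitted patients who stayed ≥ 3 days". The denominator carries no condition on carriage at admission.

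The two colonisation endpoints do carry that condition. The cumulative incidence of colonisation, listed directly above, is "divided by the number of admitted patients who stayed ≥ 3 days and were MRSA negative on admission by culture and PCR testing". The primary endpoint, under Study endpoints and statistical analysis, uses the patient-days of patients who "were MRSA negative on admission screening by conventional culture, and, if performed, PCR test".

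Three other statements bear on the point:

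- Admission swabs are taken early. In the rapid-test arm "all patients admitted to study wards will be sampled within 24 h after admission", and the control arm has the same 24 h limit.
- Contact isolation starts "as soon as newly detected by either culture or PCR", and decolonisation is given to patients positive by either method (Additional contact isolation precautions).
- The Introduction states that "MRSA colonization places the individual patient at increased risk of healthcare associated infection".

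The fourth item under Secondary aims is the rate of nosocomial MRSA infection. It is not limited to patients who acquired carriage in hospital.

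**The concern.** A cumulative incidence should count events in the same people who make up its denominator. Here the case rule suits one endpoint (infection after hospital acquisition) and the denominator suits another (any nosocomial MRSA infection in patients staying at least 3 days).

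Two things are at stake. The reported rate is diluted by patients who cannot have the event. More importantly, infections in newly detected culture-positive carriers drop out of the count. These patients are at raised risk by the Protocol's own account, and the rapid test brings forward their isolation and decolonisation. No other listed endpoint picks these infections up. If endpoints are numbered consecutively from the primary one, with the process indicators as 2 to 4, infection is endpoint 7. Secondary analysis D submits endpoint 7 to segmented regression with a hypothesised drop in level.

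**Working it through.** The Protocol states no rate, power or sample size for infection, so there is no figure to reproduce. The check is a comparison of texts, followed by illustrative arithmetic.

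**Step 1: cases against denominators.**

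| Endpoint | Case rule | Denominator |
| --- | --- | --- |
| Primary, incidence density of colonisation | first positive culture after 48 h | patient-days, stay ≥ 3 days, negative on admission |
| Cumulative incidence of colonisation | first positive culture after 48 h | patients, stay ≥ 3 days, negative on admission |
| Cumulative incidence of infection | CDC infection and first positive culture after 48 h | patients, stay ≥ 3 days, no admission condition |

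In the first two rows the phrase can only mean the patient's first positive culture. Read the same way in the third row, and dating a culture by when it was sampled, a patient whose swab within 24 h grows MRSA has a first positive culture before 48 h. That patient cannot be a case but is still counted in the denominator.

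**Step 2: inputs that the Protocol does not give (all assumptions).**

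- c, culture-positive carriage on admission: 3% to 15%
- a, infection risk in patients negative on admission: 0.5%
- b, infection risk in admission carriers: 2% to 10%

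**Step 3: dilution.** The rate as written is a(1 − c); the matched rate in admission-negative patients is a.

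- c = 3%: 0.5% × 0.97 = 0.485%
- c = 10%: 0.5% × 0.90 = 0.450%
- c = 15%: 0.5% × 0.85 = 0.425%

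The relative shortfall equals c, whatever the value of a.

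**Step 4: effect on the between-arm ratio.** The ratio is multiplied by (1 − c in the intervention arm)/(1 − c in the control arm).

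- Equal carriage: 1.00
- 8% control, 12% intervention: 0.88/0.92 = 0.957
- 5% control, 10% intervention: 0.90/0.95 = 0.947

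**Step 5: infections left out.** The share of all MRSA infections not counted is bc/[a(1 − c) + bc], with a = 0.5%.

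- c = 3%, b = 2%: 0.060%/0.545% = 11%
- c = 10%, b = 5%: 0.500%/0.950% = 53%
- c = 15%, b = 10%: 1.500%/1.925% = 78%

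**Step 6: what an effect confined to carriers would look like.** Suppose b = 5%, rapid testing halved it, and nothing else changed. The endpoint as written would show a ratio of 1.00. Counting all infections, the ratio [a(1 − c) + 0.5bc]/[a(1 − c) + bc] would be:

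- c = 5%: 0.600%/0.725% = 0.83
- c = 10%: 0.700%/0.950% = 0.74
- c = 15%: 0.800%/1.175% = 0.68

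This step treats every admission carrier as newly detected. Previously recorded carriers are not PCR tested, so including them would bring these ratios closer to 1. The halving is an illustration, not a hypothesis of the Protocol.

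**The case against.** The strongest objection is that the timing rule sits inside the parenthesis that defines a nosocomial infection. It could therefore mean the first positive culture of that infection. Carriers who later become infected would then be cases, and the wide denominator would be right. Leaving out the admission-negative condition fits that intention. This reading is open, but it gives the phrase a different meaning from the one it has in the primary endpoint and in the item directly above. The two readings give different case counts in an open-label trial, so the text still has to choose.

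Second, the objectives are faster isolation and less transmission. Infection after acquisition is a legitimate outcome of that, and the patients meant to be protected from transmission are counted. That is fair, but such an endpoint needs the admission-negative denominator.

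Third, the dilution is modest, and the same wards cross over between arms, which favours balanced carriage. This stands.

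A reader might go further and infer that infections in all patients whose care the test changes can never be counted. The documents do not support that. The rule concerns culture only: a PCR-positive, culture-negative patient is managed on the PCR result and can still be a case if a first positive culture comes after 48 h. So can a carrier missed by the admission culture or sampled late. Nor does the argument about changed care extend to previously recorded carriers, who are isolated presumptively in both arms and not PCR tested.

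**Conclusion.** The infection endpoint, as worded, mixes two populations. On the plain reading it bars patients with a positive admission culture from being cases and keeps them in the denominator, unlike the two colonisation endpoints. The rate is then understated by the factor 1 − c, which is 3% to 15% relative for assumed carriage of 3% to 15%. The between-arm ratio is unaffected if carriage is balanced, so the text alone does not show a biased treatment comparison.

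The larger consequence is that infections in newly detected culture-positive carriers go uncounted although the aim is the overall infection rate. The 11% to 78% range covers infections in all admission carriers, known and new. It rests entirely on assumed carriage and infection risks and shows only that the loss need not be small.

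This is a minor point about a secondary endpoint. The primary endpoint and the sample size are untouched.

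**What to change.** Define two rates, each with its own population:

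1. **All nosocomial MRSA infection.** State that the 48 h rule refers to the infection: CDC-defined, with onset more than 48 h after admission. Count such infections whatever the admission carriage, over all patients staying at least 3 days.
2. **Acquired MRSA infection.** Keep the rule that the patient's first positive culture comes after 48 h. Count cases in, and divide by, patients staying at least 3 days who were negative on admission, as in the cumulative colonisation endpoint.

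The existing 3-day stay rule is kept in both. The cost is a change of endpoint wording and one additional reported rate. Admission carriage status and CDC classification are already part of the planned data.
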